### Randomization and Intervention

The study design is illustrated in Figure 1. Participants will be required to be on standard-of-care, including a stable dose of angiotensin-converting enzyme inhibitors or angiotensin 2 receptor blocker for at least 30 days before randomization. Participants must have systolic blood pressure less than 180 mm Hg or diastolic blood pressure less than 90 mm Hg prior to randomization. Duke Pharmacy Investigational Drug Services will randomly assign participants 2:1 to baricitinib or placebo. According to this schema, 17 participants with FSGS will be randomized to baricitinib and 8 to placebo. Among patients with HTN-CKD, 33 will be randomized to baricitinib and 17 to placebo. We opted for this 2:1 randomization to maximize the number of patients treated with baricitinib who will support within group analyses of change in UACR over time. Baricitinib will be dose-adjusted for eGFR: 1 mg once daily orally for eGFR of 30 to 50 ml/min per 1.73 m^2^; 2 mg once daily orally for eGFR > 50 ml/min per 1.73 m^2^. The duration of treatment will be 6 months.

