
**Table 3 tbl3:** JUSTICE key exclusion criteria

1. The patient has diagnosis of diabetes mellitus.
2. The patient has biopsy-proven tip variant of FSGS.
3. The patient has history of kidney transplant.
4. The patient has sickle cell disease.
5. The patient has diagnosis of HIV or positive hepatitis B surface antigen.
6. The patient has significant liver disease with the most recent aspartate aminotransferase or alanine aminotransferase >1.5 times the upper limit of the normal range or the most recent available total bilirubin >1.5 times the upper limit of the normal range.
7. The patient has disqualifying laboratory abnormalities during screening, including hemoglobin <10 g/dl, absolute lymphocyte count <500 cells/mm^3^ or absolute neutrophil count < 1000 cells/mm^3^
8. The patient has systolic blood pressure ≥ 180 mm Hg or diastolic blood pressure ≥ 90 mm Hg.
9. The patient has current or prior history of treatment with a JAK Inhibitor.
10. The patient has active serious viral, bacteria, fungal or parasitic infection.
11. The patient has symptomatic herpes zoster infection within 12 weeks prior to study entry.
12. The patient has active malignancy.
13. The patient is pregnant, breastfeeding, or plans to become pregnant during the study period.
14. The patient, in the opinion of the investigator, is unable to comply with the requirements of the study.

FSGS, focal segmental glomerulosclerosis; JAK, Janus kinase.

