### Sample Size and Power Calculation

In Table 4, we present sample size estimates, assuming 30%, 35%, and 40% differences between baricitinib and placebo, power of 80% or 85%, different SDs for percent change in UACR from baseline to the end of month 6, and the 2:1 active:placebo randomization scheme. For the purpose of the power calculation, we assumed 0% change in UACR in the placebo arm. Assuming the higher SD of 50%, a sample of 75 participants (50 in treatment arm and 25 in placebo arm) will provide 80% power to detect a 35% decrease in UACR at month 6 compared to placebo in the overall study population with a 2-sided significance level of 5%. A total of 25 patients with FSGS and 50 patients with HTN-associated CKD will be enrolled into the study. There will be no planned interim analyses although the Data Safety and Monitoring Board will have access to unblinded results at their regularly scheduled meetings. Approval of the study design and procedures was obtained from the Duke University Institutional Review Board before enrollment. Written informed consent is obtained for participation in the study.

**Table 4 tbl4:** Sample size and power calculation

Standard deviation	Difference	Power	Required Sample size		
			Total	Baricitinib	Placebo
SD = 0.33	0.30	80%	45	30	15
		85%	51	34	17
	0.35	80%	36	24	12
		85%	39	26	13
	0.4	80%	27	18	9
		85%	30	20	10
SD = 0.50	0.30	80%	102	68	34
		85%	117	78	39
	0.35	80%	75	50	25
		85%	87	58	29
	0.4	80%	60	40	20
		85%	66	44	22

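### The pre-randomisation blood-pressure rule joins its two limits with *or*, so it does not match Table 3 item 8 and bars only patients at or above both limits

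*Protocol article*

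**What the plan says.** The article gives the blood-pressure entry rule twice.

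- **Table 3 (key exclusion criteria), item 8**, under Study Participants, states it as an exclusion: "The patient has systolic blood pressure ≥ 180 mm Hg or diastolic blood pressure ≥ 90 mm Hg". No time of assessment is given. The item just above it, item 7, does name one: "The patient has disqualifying laboratory abnormalities during screening".
- **Randomization and Intervention** states it as a requirement: "Participants must have systolic blood pressure less than 180 mm Hg or diastolic blood pressure less than 90 mm Hg prior to randomization". The sentence follows the requirement for standard of care and a stable dose of an ACE inhibitor or angiotensin receptor blocker.

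The limits, 180 mm Hg systolic and 90 mm Hg diastolic, are the same in both places. Data Collection lists blood pressure among the baseline data and adds no further eligibility rule for it.

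**The concern.** When an exclusion of the form *A or B* is turned into a requirement, both inequalities reverse and the *or* becomes *and*. Here the inequalities were reversed and the connective was not. The result is a different and much looser rule. Under item 8 each limit is enough to exclude on its own. Under the later sentence neither limit excludes anyone unless the other is reached as well.

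Two eligibility statements in one document therefore give different answers for the same reading. The looser one is worded as a *must* rule and is the only one tied explicitly to the time before randomisation. If a final check were made from that sentence alone, a patient within both limits at an earlier assessment but at 150/100 just before randomisation would pass. Blood pressure is not a peripheral criterion here: 50 of the 75 planned participants have hypertension-attributed CKD.

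**Working it through.** **Inputs.** Write S for systolic and D for diastolic pressure in mm Hg.

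- Table 3, item 8: exclude if S ≥ 180 or D ≥ 90.
- Randomization and Intervention: require S < 180 or D < 90.

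**Step 1: the requirement implied by item 8.** By De Morgan's law, not (S ≥ 180 or D ≥ 90) is the same as (S < 180 and D < 90).

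**Step 2: the exclusion implied by the later sentence.** Not (S < 180 or D < 90) is the same as (S ≥ 180 and D ≥ 90). It bars a patient only when both limits are reached.

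**Step 3: compare the rules.** The first four rows cover the four possible combinations. The last four test the boundaries.

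| Reading | Item 8 | Pre-randomisation sentence as written | Same sentence with *and* |
|---|---|---|---|
| 150/80 | pass | pass | pass |
| 185/80 | fail | pass | fail |
| 150/100 | fail | pass | fail |
| 185/100 | fail | fail | fail |
| 179/89 | pass | pass | pass |
| 180/89 | fail | pass | fail |
| 179/90 | fail | pass | fail |
| 180/90 | fail | fail | fail |

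Item 8 passes 1 of the 4 combinations and the sentence as written passes 3. They disagree on the 2 in which exactly one limit is reached. With *and*, the sentence agrees with item 8 in all eight rows.

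**Step 4: does any statistical figure depend on this?** No. The sample size uses a difference of 0.35, an SD of 0.50, 2:1 allocation, 80% power and a two-sided 5% level. The placebo arm needs (1 + 1/2) × (1.960 + 0.842)² × 0.50² / 0.35² ≈ 24.03, rounded up to 25, hence 50 + 25 = 75 as stated. Power at 50:25 is 81.5% by the normal approximation and 80.5% by the noncentral t distribution. Blood pressure does not enter this calculation.

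**The case against.** The strongest reply is that the slip admits nobody. Item 8 is an unconditional exclusion, and a patient must both meet the requirement and have no exclusion. Nothing in the article gives the later sentence precedence over Table 3, so 150/100 and 185/80 remain ineligible when the criteria are read together. This stands, and it is why the point is minor.

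The timing argument can also be challenged. Many Table 3 items carry no date, and nobody would infer that active infection or active malignancy stops excluding after screening. An undated exclusion is, if anything, broader than one limited to screening. The article describes no separate blood-pressure check just before randomisation, so the patient whose pressure rises in between is a possibility and not a documented pathway. This largely stands too. What remains is that only the faulty sentence names the time before randomisation.

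Neither place gives a reason for the limits. Calling this a safety rule is therefore an inference; the sentence could equally serve blood-pressure control ahead of an albuminuria endpoint. The point does not depend on which it is.

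Finally, the intended meaning is easy to guess, and sites would work from the full protocol, which may have it right. That limits the practical risk but does not make the published sentence correct.

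**Conclusion.** The concern holds as a minor inconsistency, with high confidence. The pre-randomisation sentence is wrong as written: it is not the complement of Table 3 item 8 and conflicts with it in 2 of 4 combinations of the two limits. That count describes logical cases, not patients; the article gives no data from which the number of patients affected could be derived. No effect on sample size, power or comparability of the arms is claimed.

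The conclusion assumes that the two statements were meant to express one rule, which the identical limits make very likely, and that item 8 states that rule correctly. Any effect on enrolment would further require that someone apply the later sentence without item 8.

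**What to change.** In Randomization and Intervention, replace *or* with *and* between the systolic and diastolic limits, so that both values must be below their limits before randomisation. The sentence then matches Table 3 item 8 in every combination and at the boundaries. The sponsor should also confirm that the full protocol and the eligibility checklist use *and*.

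The cost is one word in one sentence, with no change to design, sample size or analysis.

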## Methods

### Study Participants

Individuals aged 18 to 70 years, with biopsy-proven FSGS or clinically attributed HTN-associated CKD not due to diabetes, estimated glomerular filtration rate (eGFR) ≥25 ml/min per 1.73 m^2^ and albuminuria ≥300 mg/g, are eligible for the study if they carry APOL1 HRG. Inclusion and exclusion criteria are summarized in Tables 2 and 3. These individuals will be enrolled from clinics and the wider African American community through the Community APOL1 Research Engagement (CARE) registry (www.kidneycareandjustice.com). JUSTICE, as a part of the NEPTUNE observational study network,^32^ will also enroll participants from NEPTUNE. Individuals who self-report as Black or African American, Afro-Caribbean, Afro-Latino, or with recent African ancestry, between 18 to 70 years of age and residing in the United States are screened for history of high blood pressure, presence of albuminuria, reduced eGFR and presence of APOL1 HRG. It is possible that an individual with recent West African ancestry may be unaware of their geographical ancestry and may not self-identify as Black or African American. Therefore, if such individuals are known to carry APOL1 HRG, for instance through direct-to-consumer genetic testing, they will be eligible to screen for the JUSTICE trial, irrespective of racial or ethnic identity. It was recently reported that APOL1 G2 haplotype with a rare p.N264K single nucleotide polymorphism is protective against the risk of AMKD.^33^^,^^34^ Therefore, prospective participants with APOL1 genotypes of G1G2 or G2G2 with 1 or more p.N264K G2 haplotype will be ineligible to participate in JUSTICE. APOL1 genotype of participants entering JUSTICE is determined by using well-established Taqman based allelic discrimination or by Sanger sequencing.^21^

**Table 2 tbl2:** JUSTICE key inclusion criteria

1. The patient is willing and able to provide signed informed consent.
2. The patient resides in the United States.
3. The patient is male or female aged 18–70 years.
4. The patient has biopsy-proven FSGS or clinically diagnosed HTN-CKD
5. The patient has estimated glomerular filtration rate (eGFR) ≥ 25 ml/min per1.73 m^2^ (based on CKD-EPI Cystatin C) at screening.
6. The patient has urine albumin-to-creatinine ratio (UACR) ≥ 300 mg/g at screening.
7. The patient has high-risk APOL1 genotype of G1G1, G1G2, G2G2.
8. Patients taking antihypertensive medications must be on a stable regimen for at least 1 month prior to enrollment.

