**Figure 1 fig1:**
[figure not shown]
Flow of participants from CARE to JUSTICE. Through Community APOL1 Research Engagement (CARE) registry, community-dwelling individuals will be screened for carriage of high-risk APOL1 genotype, the presence of proteinuria, and eGFR will be measured in those with UACR ≥ 300 mg/g. Similar screening will be performed on patients with known kidney disease (FSGS or CKD without diabetes) in clinical settings. CARE participants (FSG2, *n* = 25 and hypertension-attributed CKD, *n* = 50) who have high-risk APOL1 genotype proteinuria (UACR ≥ 300 mg/g) and eGFR ≥ 25 ml/min per 1.7m^2^ will be consented for enrolment into JUSTICE trial. CBC, complete blood count; CKD, chronic kidney disease; eGFR, estimated glomerular filtration rate; FSGS, focal segmental glomerulosclerosis; LFT, liver function test; UACR, urine albumin-to-: creatinine ratio.

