### Data Collection

We will collect the following baseline data: age, biological sex, height, weight, blood pressure, eGFR, UACR, past medical and family history, current medications, previous treatments for CKD, and duration of CKD, when known, including dates of and results of kidney biopsies. The baseline and monthly eGFR will be determined with the CKD-Epidemiology Collaboration Cystatin C equation.^35^ The baseline and monthly UACR values will be the average of 2 UACR measurements based on 2 first morning voids separated by at least 2 days. Furthermore, at each monthly study visit, blood samples will be collected to measure liver function tests, serum chemistries, and complete blood counts. At each study visit when new 30-day supplies of medications will be provided, we will assess adherence by performing pill counts for the previous months and collect urine to be stored for future measurement of urinary chemokines. We will also collect data on any adverse effects. The CARE screening (visit 1) and JUSTICE screening (visit 2) visits will be in-person (Figure 2). However, participants will have the option of virtual visits for study visits 3 to 9.

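### As printed, the eligibility floor (eGFR ≥25) and the dosing rule (which starts at eGFR 30) do not meet, so an eligible participant with eGFR 25 to <30 has no stated dose.

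*Protocol article*

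**What the plan says.** **Eligibility.** The Protocol article sets the eGFR floor at 25 ml/min per 1.73 m² three times:

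- Study Participants, opening text: "eGFR) ≥25 ml/min per 1.73 m^2^ and albuminuria ≥300 mg/g, are eligible for the study", provided that they carry a high-risk APOL1 genotype.
- Table 2, item 5: "The patient has estimated glomerular filtration rate (eGFR) ≥ 25 ml/min", measured at screening with the CKD-EPI cystatin C equation.
- Figure 1 legend: those with the genotype, the albuminuria and "eGFR ≥ 25 ml/min per 1.7m^2^ will be consented for enrolment into JUSTICE trial".

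**Dosing.** Randomization and Intervention gives two bands. The lower is "Baricitinib will be dose-adjusted for eGFR: 1 mg once daily orally for eGFR of 30 to 50 ml/min"; the upper is "2 mg once daily orally for eGFR > 50 ml/min per 1.73 m^2". No readable part of the article gives a dose, a hold or a stopping rule below 30.

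**Measurement.** Data Collection says: "The baseline and monthly eGFR will be determined with the CKD-Epidemiology Collaboration Cystatin C equation". New 30-day drug supplies are handed out at study visits. The article does not say whether the dose is fixed at entry or revised as eGFR changes.

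**Status of the criteria.** The article presents them as a summary ("Inclusion and exclusion criteria are summarized in Tables 2 and 3"), and Table 3 is titled "JUSTICE key exclusion criteria".

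**The concern.** The two rules are meant to be applied one after the other: the first decides who enters, the second what an entrant assigned to baricitinib takes. Each has a numeric lower limit, and the limits differ. Someone who follows both as printed could randomize a participant whom the dosing rule does not cover.

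The gap is at the low end of kidney function. The rule halves the dose from 2 mg to 1 mg as eGFR falls, then stops short of the eligible participants with the lowest eGFR. The End Points section treats patients with CKD as possibly more vulnerable to anemia on this drug and makes a hemoglobin fall the primary safety end point. The dose for the lowest eGFR band should therefore not be left to guesswork. From the text, such a participant might receive 1 mg, receive another dose, or not be meant to enter.

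**Working it through.** No computed figure of the plan is in question. The check compares two ranges.

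**Inputs** (eGFR in ml/min per 1.73 m²)

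| Item | Range | Source in the Protocol article |
|---|---|---|
| Eligible | eGFR ≥25 | Study Participants text; Table 2 item 5; Figure 1 legend |
| 1 mg once daily | 30 ≤ eGFR ≤ 50 | Randomization and Intervention |
| 2 mg once daily | eGFR >50 | Randomization and Intervention |

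**Step 1. Range with a stated dose.** [30, 50] together with (50, ∞) gives [30, ∞). The two bands join at 50 with no gap.

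**Step 2. Eligible but without a stated dose.** [25, ∞) minus [30, ∞) = [25, 30). Width: 30 − 25 = 5. In whole numbers this is five values: 25, 26, 27, 28 and 29.

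**Step 3. Spot values.**

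| eGFR | Meets the eGFR criterion? | Stated dose |
|---|---|---|
| 24 | no | none |
| 25 | yes | none |
| 27 | yes | none |
| 29.9 | yes | none |
| 30 | yes | 1 mg |
| 50 | yes | 1 mg |
| 50.1 | yes | 2 mg |

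**Step 4. Could something else in the text close the gap?**

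- *A different eGFR equation for dosing.* Table 2 item 5 and Data Collection both name the cystatin C equation, and the dosing sentence names no other.
- *An exclusion that raises the floor.* None of the 14 items in Table 3 sets an eGFR limit.
- *A slip in one place.* The floor of 25 appears three times and consistently, so it does not look like a single misprint.
- *A dose given with the figures.* The images are not available; neither legend gives a dose.

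**Step 5. Falls during treatment.** eGFR is measured monthly. If the dose is revised on study, a participant who enters at 30 or above and later drops below 30 also has no stated dose. The article does not say whether the dose is revised, so this is conditional. It does affect the choice of remedy.

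**The case against.** The strongest reply is that an article condenses a full protocol, and dosing for a narrow renal band is the sort of detail it may leave out. The criteria are labelled as a summary of key items, the figure images cannot be seen, and the full protocol may already give a dose or a different floor. This limits the conclusion but does not remove it. The article did not leave the subject out: it printed a floor and a complete-looking dosing rule, without a qualifier on the dosing sentence, and the two disagree.

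A reader might go further and infer that the trial itself has no dose for these participants, or is dosing them unsafely. The documents do not support that. They show a disagreement between two printed ranges, not what the full protocol or the pharmacy instructions contain.

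A reader might also infer that 1 mg is obviously meant below 30. The text does not say so. Because the rule lowers the dose as eGFR falls, a further reduction or non-entry fits it just as well.

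Finally, it is fair to say that nothing statistical has been shown to suffer. That is correct, and no such claim is made.

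**Conclusion.** The point holds as an internal inconsistency in the Protocol article: a participant with eGFR from 25 to just under 30 is eligible on eGFR but has no stated dose. The uncovered band is 5 ml/min per 1.73 m² wide, set by three statements of the floor against one dosing rule. The article gives no eGFR distribution, so the number of participants affected cannot be estimated. Power, sample size and the primary analysis are not called into question.

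The conclusion rests on two things: that the readable text is all the article says about dosing, and that eligibility and dosing use the same eGFR measure, as the text indicates. It would reduce to a reporting error if the full protocol already covers the band. It should be fixed either way, because the affected participants have the lowest eligible kidney function and the introduction says that the trial has been initiated.

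**What to change.** **First, check the full protocol.** If it already sets a dose or a floor for eGFR 25 to <30, correct the article to match. The cost is a correction to the article only.

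**If it does not, choose one of two:**

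- **A. Extend the dosing rule.** Add a dose for eGFR 25 to <30, with its safety justification, and say whether it also applies when a monthly eGFR falls below 30 on study. The drawback is that the justification has to be supplied; the readable text offers none.
- **B. Raise the floor to eGFR ≥30** in the Study Participants text, Table 2 item 5 and the Figure 1 legend. Raising the floor is not enough alone: add a rule (dose, hold or stop) for on-study falls below 30 and for anyone already enrolled at 25 to <30. The drawback is a narrower eligible pool, by an amount the article does not allow one to estimate.

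**Who decides.** The blinded investigators and the sponsor, with review board approval of the amendment. The choice should not go to the Data Safety and Monitoring Board, which has access to unblinded results according to Sample Size and Power Calculation.

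**Cost.** A or B is a protocol amendment, since the trial has been initiated and its design was approved before enrollment. Neither adds a study procedure, as eGFR is already measured monthly, and neither changes the sample size calculation.

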**Figure 1 fig1:**
[figure not shown]
Flow of participants from CARE to JUSTICE. Through Community APOL1 Research Engagement (CARE) registry, community-dwelling individuals will be screened for carriage of high-risk APOL1 genotype, the presence of proteinuria, and eGFR will be measured in those with UACR ≥ 300 mg/g. Similar screening will be performed on patients with known kidney disease (FSGS or CKD without diabetes) in clinical settings. CARE participants (FSG2, *n* = 25 and hypertension-attributed CKD, *n* = 50) who have high-risk APOL1 genotype proteinuria (UACR ≥ 300 mg/g) and eGFR ≥ 25 ml/min per 1.7m^2^ will be consented for enrolment into JUSTICE trial. CBC, complete blood count; CKD, chronic kidney disease; eGFR, estimated glomerular filtration rate; FSGS, focal segmental glomerulosclerosis; LFT, liver function test; UACR, urine albumin-to-: creatinine ratio.

### Data Collection

We will collect the following baseline data: age, biological sex, height, weight, blood pressure, eGFR, UACR, past medical and family history, current medications, previous treatments for CKD, and duration of CKD, when known, including dates of and results of kidney biopsies. The baseline and monthly eGFR will be determined with the CKD-Epidemiology Collaboration Cystatin C equation.^35^ The baseline and monthly UACR values will be the average of 2 UACR measurements based on 2 first morning voids separated by at least 2 days. Furthermore, at each monthly study visit, blood samples will be collected to measure liver function tests, serum chemistries, and complete blood counts. At each study visit when new 30-day supplies of medications will be provided, we will assess adherence by performing pill counts for the previous months and collect urine to be stored for future measurement of urinary chemokines. We will also collect data on any adverse effects. The CARE screening (visit 1) and JUSTICE screening (visit 2) visits will be in-person (Figure 2). However, participants will have the option of virtual visits for study visits 3 to 9.

